## Abstract

Unhealthy diets are a critical global concern while dietary measure methods are time consuming and expensive. There is limited evidence that phone-based interventions can improve nutrition data collection and dietary quality, especially for adolescents in developing countries. We developed an artificial-intelligence-based phone application called *Food Recognition Assistance and Nudging Insights (FRANI)* to address these problems. *FRANI* can recognize foods in images, track food consumption, display statistics and use gamified nudges to give positive feedback on healthy food choice. This study protocol describes the design of new pilot studies aimed at measuring the feasibility (acceptability, adherence, and usability) of *FRANI* and its effects on the quality of food choice of adolescents in Ghana and Vietnam. In each country, 36 adolescents (12–18 years) will be randomly allocated into two groups: The intervention group with the full version of *FRANI* and the control group with the functionality limited to image recognition and dietary assessment. Participants in both groups will have their food choices tracked for four weeks. The control groups will then switch to the full version of *FRANI* and both groups will be tracked for a further 2 weeks to assess acceptability, adherence, and usability. Analysis of outcomes will be by intent to treat and differences in outcomes between intervention and control group will use Poisson and odds ratio regression models, accounting for repeated measures at individual levels. If deemed feasible, acceptable and usable, *FRANI* will address gaps in the literature and advance the nutrition field by potentially improving the quality of food choices of adolescent girls in developing countries. This pilot study will also provide insights on the design of a large randomized controlled trial. The functioning and dissemination of *FRANI* can be an important step towards highly scalable nutrition data collection and healthier food choices for a population at risk of malnutrition.

The study protocol and the methods and materials were approved by the Institutional Review Board (IRB) of the IFPRI on April 29th, 2020 (registration number #00007490), the Thai Nguyen National Hospital on April 14th, 2020 (protocol code 274/ĐĐĐ-BVTWTN) and the University of Ghana on August 10th, 2020 (Federalwide Assurance FWA 00001824; NMIMR-IRB CPN 078–19/20). The study protocol was registered in the International Standard Randomized Controlled Trial Number (ISRCTN 10681553; https://doi.org/10.1186/ISRCTN10681553) on November 12, 2021.

## Introduction

There are 1.8 billion adolescents in low- and middle-income countries (LMIC) (1). Adolescence is characterized by rapid physical growth, sexual maturation, and increased nutrient requirements (2). Meeting nutrient requirements is essential to optimize biological development, growth, long-term health, and longevity (2–4). Those who complete the physical, mental, social and emotional development of adolescence have better chances to reproduce successfully and upbring their children optimally (2). Investments to end malnutrition during this life stage are a great opportunity to interrupt intergenerational cycles of malnutrition and improve child and maternal health (5, 6).

Every year, around 16 million adolescent girls become mothers in LMIC (7). The absolute number of adolescent pregnancies is increasing, especially in settings of high prevalence of malnutrition, food insecurity and poor dietary quality such as Africa, South Asia and Southeast Asia (2). Both under and overnutrition before and during pregnancy predict altered growth and health of the offspring (8). Pregnant adolescents typically compete for nutrients with the fetus, increasing risk of low birthweight and short birth length (9, 10). The risk of preterm delivery, and poor childhood growth and nutritional status is also higher for neonates of adolescent mothers (11, 12).

Solutions to maternal and child malnutrition in LMIC have to take into account the social and cultural factors that drive adolescent decision making (5, 13, 14). Adolescent neuro-development make them more aware of external influences, preferences and habits of peers and family (15, 16). This increases the desire to have social recognition, status, and autonomy (17–19). Responsibility over food acquisition, preparation, and consumption start in adolescence (6). The sensitivity to external influence coupled with greater power for food choice (20) create a unique opportunity to foster long-term healthy eating (6).

Data collection for adolescent nutrition is fundamental to design effective policies and programs and to assess their progress (5, 6, 13). The Nudging for Good project aims at developing, validating and examining the feasibility of the Food Recognition Assistance and Nudging Insights (FRANI), a phone application that uses artificial intelligence technology to recognize foods in pictures, assess diets and nudge adolescents from Ghana and Vietnam to make healthier food choices (21). First, we made food inventories, prepared and cooked these foods, weighted, annotated and took pictures of them. We linked the pictures to food composition tables, and built models to recognize the images and estimate portion sizes. Finally, we developed the interface according to the preferences showed in focus groups discussions by adolescent girls from Ghana and Vietnam. We validated the FRANI dietary assessment through food image recognition against the gold standards of weigh food records and 24 h recalls. Now, we aim at conducting a randomized controlled pilot study to measure the feasibility of using FRANI and its impact on the quality of food choice.

### The intervention

The FRANI mobile app is designed to improve diets by increasing the consumption of healthy foods and beverages, whilst crowding out the consumption of energy-dense foods. FRANI users can set healthy eating goals – or choose daily dietary goals from a list of simple options based on food groups, such as “have a dark green vegetable” or “eat a whole grain”. Conceptually, this increases motivation and interest in learning about healthy diets, as well as increases awareness of what are healthy and unhealthy foods. Alongside individual-based goals, users can opt-in to team-based goals that may lead to stronger peer support on healthy eating practices and provide social praise for healthier food choices. However, in order to avoid peer-pressure, users can only visualize team progress as a whole and cannot track the individual performance of peers.

FRANI provides feedback based on the information uploaded by users, or on the pictures of foods and beverages they consume. The AI technology is trained on a database of calibrated images with foods and beverages to enable estimation of both the foods and portion sizes in the uploaded pictures. FRANI then coverts the food quantities into nutrients by using food composition tables. The practicality of this technology has the potential to increase the frequency of data points collected on food consumption, addressing the constraint faced by common diet estimation methods with regards to estimating usual intake (22).

## Methods and analysis

### Materials

The pilot studies are based on two-armed randomized controlled designs to be implemented in Ghana and Vietnam. In each country, 36 adolescents (12–18 years) will be randomly allocated into two groups: The intervention group with the full version of FRANI, including diet records and nudges to encourage healthier food choices. The control group will receive mobile phones with FRANI functionality limited to the dietary assessment. Participants in both groups will have their food choices tracked for a four week period. The control group will then switch to also use FRANI with full functionality and both groups will be tracked for a further 2 weeks to assess acceptability, adherence, and usability. The schedule of the intervention, enrollment and assessment is described in Figure 1. The stylized program impact pathway for the intervention is described in Figure 2 (21).

**Figure 1 F1:**
[figure not shown]
Adapted SPIRIT diagram (29). Schedule of enrolment, interventions, and assessments of the two-armed randomized controlled pilot studies in Ghana and Vietnam. *The participants in the control group will use FRANI with limited functionality to track their food choices for 28 days (4 weeks). After that, the control group will switch to also use FRANI with full functionality for the last two weeks of the post-allocation period. The bullet in t28 indicates that the control group switched for the full version app.

**Figure 2 F2:**
[figure not shown]
The stylized program impact pathways for the FRANI. (Source: Adapted from (21)) Notes: Yellow represents the two steps users have to follow to have their dietary consumption tracked and to be nudged to make healthier food choices. Green boxes show nudges to influence the use of the FRANI and healthy food choices. Blue boxes represent what is expected to improve with the FRANI use. Gray is for a possible unintended consequence of the FRANI use that should be fixed in future versions of the app.

The main differences in the application versions for the intervention and control groups are described in Table 1. Briefly, both the intervention and control versions of FRANI recognize food images, assess the quality of the user's diet, and receive notifications with reminders to take pictures. However, only the treatment group can set food consumption goals, see the home screen, scores and statistics about dietary quality, receive badges and receive a daily report summarizing everything they ate in that day.

**Table 1 T1:** Features of FRANI by intervention group in the first four weeks of the pilot study.

Feature	Intervention	Control
Meal entry (picture taking)	X	X
Recognize food image in pictures	X	X
Assess quality of user's diet	X	X
Notifications	X	X
Setting goals	X	NA
Home screen	X	NA
Scores and statistics	X	NA
Medals and badges	X	NA
Daily report	X	NA
Activity feed	X	Modified
Daily report	X	NA

NA, not available. At the end of the fourth week, the control group switches to the intervention version and all participants use the same version of FRANI for two weeks to measure adherence, acceptability and usability.

The options for setting food consumption goals were based on the EAT-Lancet Diet (23) and the Dietary Guidelines of Vietnam (24). These FRANI goals can be individual- or team-oriented, and involve five main food groups: (1) grains and starchy staples; (2) legumes, nuts and seeds; (3) fruits and vegetables; (4) dairies; (5) animal-source foods (excluding dairy). In addition to setting food consumption goals, participants from the intervention group be nudged with game elements. These nudges include: (1) tracking progress towards healthy-eating goals; (2) giving personalized feedback on food consumption; (3) reinforcing healthy food consumption; (4) tracking progress in the quality of food consumption with statistics; (5) participating in goals shared with other users (team-based goals); (6) sharing positive feedback with peers. Participants in the intervention group will be able to choose from team-based goals on a weekly basis. They will receive information about their team's overall performance but in order to avoid excessive peer pressure they will not be able to see each individual team member's performance.

The study protocol and the methods and materials were approved by the Institutional Review Board (IRB) of the IFPRI on April 29th, 2020 (registration number #00007490), the Thai Nguyen National Hospital on April 14th, 2020 (protocol code 274/ĐĐĐ-BVTWTN) and the University of Ghana on August 10th, 2020 (Federalwide Assurance FWA 00001824; NMIMR-IRB CPN 078–19/20). The study protocol was registered in the International Standard Randomized Controlled Trial Number (ISRCTN 10681553; https://doi.org/10.1186/ISRCTN10681553) on November 12, 2021. Participants will be instructed to report any problem occurring during the study to the country-lead researchers, which will be in direct contact with them. Although risk from using FRANI is minimal, any adverse effect will be discussed by the team, and reported to the IRB of the IFPRI and to the ethics boards of correspondent countries. All procedures were and will be in accordance with the Declaration of Helsinki.

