### Randomization and allocation

A computer-generated random number will randomize participants in the intervention and control groups at a 1:1 ratio for each country separately. The allocation sequence will be generated and the enrollment and assignment will be done by the senior researchers of the Vietnamese and Ghanaian teams. Although a similar description of FRANI will be presented for intervention and control groups in the process of informed assent and consent, it will not be possible to blind who is receiving feedback from FRANI and who is not. The data will be collected by the application without assessors.

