### Outcomes

The feasibility of FRANI will be assessed by measuring outcomes related to adherence, acceptability, and usability as summarized in Table 2 (25, 26). According to the World Health Organization (WHO), adherence is “the extent to which a person's behavior – taking medication, following a diet, or executing lifestyle changes, corresponds with agreed recommendations from a health care provider” (27). Although there is no consensus in the literature on the best measure for adherence to eHealth technology interventions (25, 26), maximum benefit from the intervention as defined by creators should be considered (28). We define the sample adherent to FRANI if 70% or more of participants-days upload complete dietary recalls in the last two weeks of the pilot study. Acceptability summarizes likeability and satisfaction with FRANI, while usability summarizes what affects the use of the FRANI. Acceptability and usability are measured according to answers from structured questionnaires described in Table 3. If participants grade the acceptability or usability of FRANI as 30 or less points in their respective structured questionnaires, the app will be considered accepted or usable.

**Table 2 T2:** Domains and outcome measures for the FRANI pilot test.

Outcomes	Definition
Primary outcomes (feasibility)	
Adherence	The number of days participants upload completed dietary recalls on the FRANI divided by the total number of dietary recalls (complete + incomplete) of the last two weeks of the pilot test is equal to or higher than 70%
Acceptability	Summarizes likeability and satisfaction with FRANI according to answers from a structured questionnaire. If participants grade the acceptability of FRANI as 30 or less points on a scale from 10 to 50 points, the app will be considered accepted.
Usability	Summarizes possibility to use and intent to keep using FRANI according to answers from a structured questionnaire. If participants grade the usability of FRANI as 30 or less on a scale from 10 to 50 points, the app will be considered usable.
Secondary outcomes	
Percentage of meals recorded	The number of meals recorded on the FRANI divided by the number of total meals participants had during the last two weeks of the pilot test period.
Dietary Diversity Score^a^	Ranges from 0 to 10 points using MDDW dietary diversity food groups (daily score) measured in the first four weeks of the pilot study period.

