### Sample size

The sample size was determined by the number of smartphones and data packages that could be supported by budget and is consistent with other pilot studies in the literature. The effect size of the treatment on the DDS and the SHDS on the first four weeks of the study will be used to calculate the sample size of a larger experiment.

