### Statistical analysis

The data from the pilot studies from Ghana and Vietnam will be analyzed and reported separately, though a pooled analysis will also be undertaken once both pilots have been completed. The analysis will be by intent to treat, and we do not expect to have loss of follow-up as this is a small scale pilot. Descriptive statistics and balance tables will be calculated for all variables and will be presented as medians or means with standard deviations. Differences in the outcomes between intervention and control groups will be estimated by multi-level Poisson regression models with the DDS and the SHDS as outcomes, a dummy variable for the treatment, a continuous time variable for the days and an interaction of treatment and time, and random effects at the individual level to account for the repeated measures. We will also undertake exploratory analysis for each food group of the DDS and the SHDS separately using odds ratio regressions. Socio-demographic variables that were not balanced after randomization will also be included in the robustness analysis.

A *p*-value < 0.05 will be considered statistically significant and *p*-value < 0.1 will be considered marginally significant. We will assess the need to screen outliers values greater than three standard deviations and will analyze the sensitivity of the treatment effect to the outliers.

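### Recording is measured only in weeks 5–6, when both arms use the full app, so no defined outcome shows whether it differs between arms during the weeks 1–4 diet comparison

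*Protocol article*

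**What the plan says.** The only document at hand is the protocol article.

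- **Design (Materials, Figure 1 legend, Table 1).** For four weeks the intervention arm has the full app. The control arm has a version without goals, home screen, scores and statistics, badges or daily report. The note under Table 1 then says that "the control group switches to the intervention version and all participants use the same version of FRANI for two weeks to measure adherence", and also acceptability and usability.
- **Recording measures (Outcomes, Table 2).** The sample counts as adherent if at least 70% of participant-days "upload complete dietary recalls in the last two weeks of the pilot study". Percentage of meals recorded, a secondary outcome, has the same two-week window.
- **Diet measures (Table 2).** DDS and SHDS are daily scores from the first four weeks. The text after Table 3 says that they, like adherence and meals recorded, come from data captured by the app.
- **Comparison between arms (Outcomes, text after Table 3).** The effects of the app and its nudges are to be judged on secondary outcomes, with percentage of meals recorded named among them. Secondary outcomes rest on comparing the arms; primary ones do not.
- **Use of the result (Sample size).** "The effect size of the treatment on the DDS and the SHDS on the first four weeks" will be used to calculate the size of a larger experiment.

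**The concern.** The app is both the treatment and the instrument that measures diet. The Figure 2 legend describes the nudges as meant to influence use of the app as well as food choice. If they work on use, they raise recording in one arm only, in exactly the weeks when recording produces the outcome. A girl who photographs fewer of her meals shows fewer food groups and scores lower, whatever she ate.

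The one secondary outcome that could expose this, percentage of meals recorded, is taken only after the control arm has received the nudges. In weeks 5–6 it can compare girls who have had the full app for longer with girls who have just switched. It cannot compare the two versions in concurrent use, although the Outcomes text says secondary outcomes rest on comparing the arms.

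At stake is the reading of the DDS and SHDS contrast, and of the effect size taken from it. An effect inflated by recording would make the larger trial too small; one masked by it would make that trial too large or discourage it.

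**Working it through.** The sample size was set by budget, so the plan has no power figure to reproduce. The check counts girl-days and then shows how unequal recording could act.

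**Inputs from the protocol.** "In each country, 36 adolescents (12–18 years) will be randomly allocated into two groups" (Materials); the sequence will "randomize participants in the intervention and control groups at a 1:1 ratio for each country separately" (Randomization and allocation), so 18 per arm. The limited version runs for 28 days and the recording window for 14.

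**Girl-days per country**
- Weeks 1–4, limited version: 18 × 28 = 504.
- Weeks 1–4, full version: 18 × 28 = 504. The DDS/SHDS contrast thus rests on up to 1,008 girl-days, half on the limited version.
- Weeks 5–6: 36 × 14 = 504, all on the full version; 70% of these is 353 days, rounded up.
- Limited-version days inside the recording window: 0.

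Pooled over both countries there are 1,008 limited-version days, again none inside the window.

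**Illustration 1: meals missing within a day.** Assumptions, none from the protocol: four eating occasions a day, each of 10 food groups eaten on 50% of days, meals recorded independently, no true diet effect. The chance *q* that a group appears at one meal solves 1 − (1 − q)⁴ = 0.5, so q = 0.159. With a share *r* of meals recorded, recorded DDS = 10 × [1 − (1 − q·r)⁴]. The full-version arm is held at r = 0.90, giving 4.61.

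| Control r | Control DDS | Apparent ratio |
|---|---|---|
| 0.90 | 4.61 | 1.00 |
| 0.80 | 4.20 | 1.10 |
| 0.70 | 3.76 | 1.23 |
| 0.60 | 3.31 | 1.40 |
| 0.50 | 2.82 | 1.63 |

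**Illustration 2: whole days missing.** The shift in the contrast of recorded means equals the gap in unrecorded share times the difference in score between recorded and unrecorded days. If that difference is 1 DDS point, each 10-point gap in recording shifts the contrast by 0.10 × 1 = 0.10. With 80% against 50% of days recorded, 101 against 252 of 504 days are missing and the shift is 0.30 × 1 = 0.30. The direction depends on whether unrecorded days score higher or lower, which is unknown.

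**Precision of a by-arm recording measure.** Assume a mean share of 70%, so a daily variance of 0.7 × 0.3 = 0.21, and a within-girl correlation *ρ*. The SD of a girl's 28-day share is √[0.21/28 × (1 + 27ρ)], which is 0.22, 0.30 and 0.36 for ρ = 0.2, 0.4 and 0.6. The half-width of the 95% interval for the arm difference is 1.96 × SD × √(2/18): 14.3, 19.4 and 23.5 points per country. With 36 per arm it is 10.1, 13.7 and 16.6 points.

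**The case against.** **The window suits its purpose.** Feasibility concerns the full app, the switch exists so that everyone is assessed on one version, and the primary measures are expressly not compared between arms. This stands: the adherence definition is not wrong, and the gap lies beside it. It does not cover percentage of meals recorded, a secondary outcome meant for comparison between arms.

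**The data will exist, and an analysis plan may use them.** Records upload in real time, descriptive statistics are planned for all variables, and local teams follow participants throughout. So it would be too strong to say that recording on the limited version cannot be known. But Table 2 fixes the window of both recording measures, and that window does not fit the Outcomes text; this is not detail left to another document.

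**Differential recording is not shown.** True. Control girls get the same reminders and a modified activity feed, and no figure in the protocol points to a gap. The numbers above show what a gap would do, not that there will be one. The random-effects model may also absorb some missingness that depends on observed scores. It cannot recover meals missing from a scored day.

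**Weeks 5–6 are not blind to lasting disengagement.** Control girls supply half of those girl-days. If 80% and 50% recording persisted, overall adherence would be (80 + 50)/2 = 65%, a fail. With the intervention arm at 80%, a pass needs control girls at 60% or more after switching. So a pass despite poor control recording in weeks 1–4 is possible, but only with such a rebound.

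**Two stronger readings that a reader might infer**
- That the larger trial will use the limited app as its comparator. The protocol ties that trial to this contrast only through the effect size; it names no comparator.
- That "we do not expect to have loss of follow-up as this is a small scale pilot" contradicts the 70% mark. It does not: the sentence concerns girls leaving the study, the mark concerns complete recalls, and a girl can stay in the study with incomplete days.

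**Conclusion.** The point holds as a gap in the outcome set that should be closed. No defined outcome shows whether recording differs between arms in weeks 1–4, and percentage of meals recorded has a window that cannot deliver the comparison of versions which the Outcomes text implies. The unmonitored part is 504 of the 1,008 girl-days per country behind the DDS/SHDS contrast. That count follows from the protocol alone.

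The size of any bias is unknown. The apparent ratios of 1.10 to 1.63 and the shift of 0.10 DDS points per 10-point gap rest on the assumptions stated above. Meals missing within a day would favour the full-version arm if control girls record less; whole missing days could push either way.

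A rule keeping the limited version for the larger trial only if its own recording reaches 70% is not warranted. Bias depends on the gap between arms: on the whole-day formula, 95% against 70% would pass with a 0.25-point shift, while 65% against 65% would fail with none. With 18 girls per arm the rule would also be noisy.

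**What to change.** Keep the weeks 5–6 feasibility criterion as it is, and make three additions.

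1. **In Table 2, recording in days 1–28, by arm:** complete-recall days out of 28, with all randomised girls in the denominator so that days with nothing uploaded count, and meals recorded. Give the between-arm difference with a 95% interval computed at girl level.
2. **In Statistical analysis:** a sensitivity analysis of the DDS and SHDS contrast that shifts the scores of unrecorded days by a stated amount (for example −1, 0 and +1 point), separately by arm.
3. **In Sample size:** say that the weeks 1–4 effect size will be read alongside both results before it is used to size the larger experiment.

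Complete-recall days need no new fieldwork, because the app uploads records in both arms. For meals recorded as a percentage, the total number of meals must be obtained in weeks 1–4 in the same way as in weeks 5–6; otherwise report recorded meals per girl-day. The price is a little more analysis and wide intervals: about ±14 to ±23 points per country and ±10 to ±17 pooled, under the assumed correlations of 0.2 to 0.6. That would reveal a large gap but not exclude a modest one, which is why the sensitivity analysis is needed as well.

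### The DDS and SHDS model has no term for teams: if team mates' diets correlate, the standard error of the four-week average effect will be too small

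*Protocol article*

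**What the plan says.** The section on the intervention says that "users can opt-in to team-based goals that may lead to stronger peer support on healthy eating practices". The Materials section lists the nudges for the intervention group, including "participating in goals shared with other users (team-based goals" and "sharing positive feedback with peers". It adds: "Participants in the intervention group will be able to choose from team-based goals on a weekly basis". Of team feedback it says: "They will receive information about their team's overall performance"; the results of individual members stay hidden.

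The text introducing Table 1 says that "only the treatment group can set food consumption goals". The table marks goal setting as not available to controls, and their activity feed as modified, for the first four weeks. Table 2 measures DDS and SHDS as daily scores over those same four weeks.

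Allocation is by individual, 1:1 within each country. Statistical analysis specifies "multi-level Poisson regression models with the DDS and the SHDS as outcomes", with treatment, day and their interaction, and "random effects at the individual level to account for the repeated measures". P-values are judged at 0.05, and at 0.1 as marginal. Under Sample size, the DDS and SHDS effects are to be used in sizing a larger experiment.

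**The concern.** Part of the intervention is meant to work through peers. Girls in one team can pursue the same food-group goal and see the same team result, and both outcomes are counts over food groups. That is a reason to expect team mates' scores to be more alike than those of girls in different teams, and for team goals this can arise only in the intervention arm. The random effect for the girl handles repeated days within her; it does nothing for correlation between girls. If that correlation is positive, the model credits the intervention arm with more independent information than it has. A result could then cross 0.05 or 0.1 because its error is understated, and the planners of the larger trial would have no basis for a clustering allowance.

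**Working it through.** The plan has no figure to reproduce: the sample size was set by budget, and no power, ICC or team size is given. The size of the problem therefore has to be shown over a range.

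**From the protocol:** 36 girls per country at 1:1, so 18 per arm (36 per arm pooled); 28 daily scores per girl; alpha 0.05.

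**Assumed:** a two-sided test; equal teams of size m in the intervention arm; ICC is the correlation between team mates' four-week person-level scores; controls independent; equal variance in the two arms.

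**Formulas.** With n girls per arm and between-girl variance σ²:

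- Planned model: Var(difference) = 2σ²/n.
- With teams in one arm: Var(difference) = (σ²/n)[1 + (m−1)ICC] + σ²/n.
- True/reported standard error = √{[2 + (m−1)ICC]/2}.
- Actual alpha = 2[1 − Φ(1.96/ratio)].

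Worked case, m = 6 and ICC = 0.10: ratio = √(2.5/2) = 1.118; 1.96/1.118 = 1.753; alpha = 0.080. The 18 intervention girls then carry the information of 18/1.5 = 12.

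| Team size | ICC | SE ratio | Alpha, formula | Alpha, simulated t-test, 18 per arm |
|---|---|---|---|---|
| 3 | 0.05 | 1.02 | 0.056 | 0.056 |
| 3 | 0.10 | 1.05 | 0.062 | 0.064 |
| 3 | 0.20 | 1.10 | 0.074 | 0.074 |
| 6 | 0.05 | 1.06 | 0.065 | 0.070 |
| 6 | 0.10 | 1.12 | 0.080 | 0.080 |
| 6 | 0.20 | 1.22 | 0.110 | 0.114 |
| 9 | 0.05 | 1.10 | 0.074 | 0.074 |
| 9 | 0.10 | 1.18 | 0.098 | 0.100 |
| 9 | 0.20 | 1.34 | 0.144 | 0.152 |

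Simulations used 20,000 runs per setting. Pooling the countries does not remove the inflation: with 36 per arm, m = 6 and ICC 0.10 again gives 0.080. Outside the table, pairs at ICC 0.01 give 0.051. A single team of 18, which the text does not exclude, gives 0.101 at ICC 0.05 and 0.150 at ICC 0.10.

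**Check on a model of the planned type.** A Poisson model with an individual random intercept (gamma), treatment, day centred at mid-period, and treatment by day was fitted to 36 girls over 28 days, 600 runs per setting. Scores were generated either as binomial out of 10 or as Poisson.

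- Average effect: alpha was 0.047 (binomial) and 0.067 (Poisson) without team correlation, and 0.107 and 0.095 at m = 6, ICC 0.10.
- Treatment by day, binomial scores: 0.003 to 0.008 without team differences in slope, 0.023 to 0.028 with modest ones, 0.165 with large ones.
- Treatment by day, Poisson scores: 0.030 to 0.057 without team slopes, 0.072 to 0.192 with them.

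So the average effect moves as the formula predicts. The interaction has no fixed direction, because Poisson variance overstates the spread of a bounded score.

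**The case against.** The strongest reply is that the documents leave the dependence open. Team goals are opt-in, goals may also be individual, members do not see each other's results, and size, uptake and ICC are all unstated. This stands: the claim must be conditional, and at the low end the inflation is trivial.

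A second reply is that an article may leave sensitivity analyses to a fuller plan. That would settle it if the article were silent on the model. It is not: it states the random-effects structure and the reason for it, and that structure leaves out a dependence that the intervention is built to encourage.

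A third is that the planned model includes treatment by day, and much of any effect may sit in that term. This also stands. A reader might infer that every DDS and SHDS p-value is too small; the checks support this only for the average effect.

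A reader might also infer that a distorted effect is carried into the larger trial. The protocol says that the effect size is carried forward, and ignoring teams does not bias the point estimate. Between-girl variance is barely touched: in the intervention arm it is low by (m−1)ICC/(n−1), which is 0.5/17 = 3% at m = 6, ICC 0.10 and 1.6/17 = 9% at m = 9, ICC 0.20. Pooled over two arms, these halve.

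Finally, restriction to one arm is clear for team goals but less so for shared feedback, since the control feed is modified and not described as absent. All girls in a country also come from one school, so independent controls are an assumption.

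**Conclusion.** The point holds conditionally. The model as stated has no place for correlation between team mates, and if that correlation is positive, the standard error and p-value of the four-week average effect on DDS and SHDS will be too small. Over the assumed range (teams of 3 to 9, ICC 0.05 to 0.20) the understatement is a factor of 1.02 to 1.34 and the actual error rate is about 0.06 to 0.15. The upper end needs two teams of nine at the highest ICC; at ICC 0.05 the rate is 6% to 7%. The documents do not support saying that the standard errors are too small whatever the teams turn out to be. The arm comparison is secondary, and the primary feasibility measures do not use it. Severity is minor to moderate.

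**What to change.** Keep the planned model. Retain team membership by week from the app, since goals are chosen weekly and the protocol does not say that teams stay fixed. Pre-specify one sensitivity analysis of the four-week average treatment effect that allows for team correlation in the intervention arm only, treating each control, and each intervention girl who joins no team, as a cluster of one. Because day and its interaction are in the model, define the average effect as a contrast over the four weeks; the treatment coefficient alone depends on how day is centred.

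Show the interval at fixed ICCs, for example 0.05, 0.10 and 0.20, and label them as assumptions. Estimating the ICC is not a realistic alternative: three teams of six estimate the team variance poorly, and a single team cannot estimate it at all. Read p-values near 0.05 and 0.1 in the light of these intervals.

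If the larger trial keeps teams, multiply its total sample by about 1 + (m−1)ICC/2: 1.05 at m = 3, ICC 0.05; 1.25 at m = 6, ICC 0.10; 1.80 at m = 9, ICC 0.20.

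The cost is a short added analysis, with more care needed if membership changes from week to week, somewhat wider intervals, and a somewhat larger stated size for the next trial.
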